### Measurements

Baseline data will be obtained from the PHS and the additional questionnaire. Six months after inclusion, a follow-up measurement will take place. Twelve months after inclusion, the second follow-up measurement will take place.

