#### Biomedical variables

BMI (kg/m^2^), systolic and diastolic blood pressure (mmHg), HDL-cholesterol, total cholesterol (mmol/l) and HbA1c (%) will be assessed by an occupational nurse at the PHS. First, weight will be measured on a digital balance, without shoes and jacket. After that, blood pressure will be measured once, by manual inflation, while the worker is seated. In most OHSs, a Maxi Stabil 3 measuring instrument (Speidel & Keller) will be used for this purpose. Finally, for the determination of HDL-cholesterol, total cholesterol and HbA1c levels venous blood will be drawn from the lower arm and transported to the laboratory for analysis. For each of these 3 measures 1.6 ml blood will be used. As described in the introduction, elevated BMI, blood pressure and cholesterol are indicators of CVD risk. HbA1c, a measure of haemoglobin glycosylation, is an indicator of the mean blood glucose level of the past 6–8 weeks [47]. Elevated HbA1c was shown to be an independent risk factor for coronary heart disease in persons with and without diabetes [48].

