#### Cost-effectiveness

Next to investigating the effects of the intervention, the costs of the intervention will be compared to the effects. All costs for the development of the intervention, i.e. training and printing of brochures, as well as for the implementation of the intervention, i.e. (previously defined) reimbursements for participant's travelling expenses, counsellor's face-to-face and telephone contacts and occupational nurses' health checkups, will be recorded by the principal investigator. Incremental costs of the intervention group compared to the control group will be divided by incremental effects for each of the biomedical effect measures, e.g. BMI, total cholesterol and systolic blood pressure, separately.

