### Data analysis

On all outcome measures, intention-to-treat analyses will be performed. Both crude and adjusted linear and logistic regression analyses will be performed. In doing so, analysis for covariance will be conducted adjusting for the outcome variable measured at baseline. In the adjusted model, other potential confounders will be included as covariate, such as age and work activities. Furthermore, effect modification, e.g. by family history, will be checked. First of all, data will be analysed for the whole intervention group, that is, irrespective of the intervention received. Secondly, subgroup analysis will be done among those having received the smoking or the energy balance intervention. As all participants will have to indicate at baseline which lifestyle behaviour they prefer to change, the participants in each intervention subgroup will be compared to those in the control group having indicated the same type of intervention preference. Cost-effectiveness ratios will be calculated by dividing the difference between the mean total costs between the two study groups by the difference in the mean effects. For each outcome measure used in this evaluation, cost-effectiveness ratios will be presented graphically on a cost-effectiveness plane. To calculate the confidence intervals for the ratios, bootstrapping will be done. For all analyses, a significance of 0.05 will be applied. On the process evaluation, qualitative analyses will be performed.

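### The cost-effectiveness denominator is not tied to the baseline-adjusted effect estimate; read literally, it is an unbiased but less precise difference that can disagree with the reported effect

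*Protocol article*

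**What the plan says.** The protocol article (Data analysis) describes the effect analysis first. "Both crude and adjusted linear and logistic regression analyses will be performed", and within these "analysis for covariance will be conducted adjusting for the outcome variable measured at baseline". Further covariates enter a second model: "In the adjusted model, other potential confounders will be included as covariate, such as age and work activities".

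The same section then turns to the economic evaluation: "Cost-effectiveness ratios will be calculated by dividing the difference between the mean total costs between the two study groups by the difference in the mean" (that is, in mean effect). Intervals are by resampling: "To calculate the confidence intervals for the ratios, bootstrapping will be done". The section on cost-effectiveness names the effects concerned. Incremental costs are "divided by incremental effects for each of the biomedical effect measures, e.g. BMI, total cholesterol and systolic blood pressure, separately".

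These measures exist before randomisation. Under Measurements, "Baseline data will be obtained from the PHS and the additional questionnaire", where PHS is the periodical health screening. Under Biomedical variables, BMI, blood pressure, cholesterol and HbA1c "will be assessed by an occupational nurse at the PHS".

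Neither section says whether the denominator is the covariance-adjusted difference, the difference in mean change, or the difference in follow-up means. Neither calls it unadjusted.

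**The concern.** The ratio has its own formula, and the wording for numerator and denominator is parallel: a difference between two group means over another such difference. An analyst who follows it literally would compute an unadjusted difference in BMI, cholesterol or blood pressure, a few lines after the same section has adjusted those outcomes for baseline.

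Two things follow. First, the denominator is noisier than it need be. A ratio is sensitive to noise in a small denominator, and extra noise spreads the bootstrap replicates along the effect axis of the cost-effectiveness plane. Second, the effect on that plane can differ from the effect reported for the same outcome in the same trial. The Discussion links possible wider use by the occupational health services to proof of cost-effectiveness, so the ratio has a reader.

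**Working it through.** **Inputs.** The plan states no figure for this point that could be reproduced. The group size is 346 per arm (Sample size calculation), the number the plan wants after loss to follow-up. That figure does reproduce: 38% against 28%, two-sided 0.05, 80% power, pooled-variance formula without continuity correction, gives 346 per arm and 692 in total. The baseline to follow-up correlation ρ is not given, so 0.5, 0.7 and 0.9 are assumed. Equal variances at both times and a common SD are also assumed, and effects are expressed in SD units.

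**Standard error of each candidate denominator.**

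- Raw follow-up means: √(2/346) = 0.0760.
- Mean change from baseline: 0.0760 × √(2(1 − ρ)).
- Baseline-adjusted difference: 0.0760 × √(1 − ρ²).

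| ρ | Raw means | Mean change | Adjusted | Raw ÷ adjusted | Change ÷ adjusted |
|---|---|---|---|---|---|
| 0.5 | 0.076 | 0.076 | 0.066 | 1.15 | 1.15 |
| 0.7 | 0.076 | 0.059 | 0.054 | 1.40 | 1.08 |
| 0.9 | 0.076 | 0.034 | 0.033 | 2.29 | 1.03 |

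The ratios are 1/√(1 − ρ²) for raw means and √(2/(1 + ρ)) for mean change. They do not depend on the group size. The loss grows with ρ for raw means and shrinks with ρ for mean change.

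**Chance that the denominator has the wrong sign.** Take an assumed true effect of 0.1 SD (the documents give none). The probability is Φ(−0.1/SE).

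| ρ | Raw means | Mean change | Adjusted |
|---|---|---|---|
| 0.5 | 9.4% | 9.4% | 6.4% |
| 0.7 | 9.4% | 4.5% | 3.3% |
| 0.9 | 9.4% | 0.2% | 0.1% |

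**How far the two effects can differ.** In large samples the raw and adjusted estimates differ by ρ times the chance baseline imbalance, so the SD of their difference is ρ × 0.0760. At ρ = 0.7 this is 0.7 × 0.0760 = 0.053 SD. For mean change it is (1 − ρ) × 0.0760 = 0.3 × 0.0760 = 0.023 SD.

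A simulation of 3,000 trials with 346 per arm, ρ = 0.7 and an assumed effect of −0.15 SD gave 0.052 and 0.022. The raw and adjusted estimates had opposite signs in about 2% of trials, and the change and adjusted estimates in 0.5%. The average estimates were −0.152 (raw), −0.151 (change) and −0.151 (adjusted), so all three are centred on the true effect.

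**The case against.** The strongest reply is that the plan never says the denominator is unadjusted. The Data analysis section opens by covering all outcome measures, and the section on cost-effectiveness speaks of comparing costs with the effects of the intervention. Taking those effects from the analysis of covariance fits the wording. A condensed article may also leave the estimator to a fuller document. This stands in part. A reader might infer that the plan fixes an unadjusted denominator, and the documents do not support that. They give a formula that omits the link.

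Second, if the denominator is unadjusted, mean change is arguably the more natural sense of an effect than a follow-up level. The loss is then small when the correlation is high. This stands, and it limits the size of the point.

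Third, a reader might infer bias. There is none: with individual randomisation all three differences estimate the same effect. A change score over-corrects only in the sense of its behaviour given an observed baseline imbalance.

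Fourth, a reader might infer lost power. No test on the denominator is planned, and the sample size concerns physical inactivity, so power figures for these measures would correspond to nothing in the plan.

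Finally, the Discussion says only that services may implement the intervention if it is cost-effective. The firmer statement in the abstract depends on effectiveness, which the effect analysis decides.

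The objection does not remove the point. The article chose to print a formula, that formula does not carry the adjustment described just before it, and a better estimator is available from data already collected.

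**Conclusion.** The point holds as a low-severity improvement in precision and consistency. The denominator of the ratio is not linked to the baseline-adjusted effect. If it is computed as written, its standard error exceeds that of the adjusted estimate by about 15% to 129% for raw follow-up means, or about 15% down to 3% for mean change, as ρ goes from 0.5 to 0.9. The effect on the cost-effectiveness plane could then differ from the reported one, typically by about 0.05 SD (raw means) or 0.02 SD (mean change) at ρ = 0.7.

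These sizes rest on assumed correlations, equal variances and 346 analysed per arm. The wrong-sign probabilities rest further on an assumed effect of 0.1 SD. If the sponsor already intends the adjusted difference, nothing is lost except that the text does not say so.

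**What to change.** In Data analysis, state that the denominator of each ratio is the baseline-adjusted between-group difference from the linear model used in the effect analysis. Because a crude model and a model with further covariates are both planned, name which of the two supplies it. State also that this model is refitted in every bootstrap replicate, with each participant's costs and effects resampled together within arm. The effect axis of the plane then matches the reported effect, and the interval keeps the correlation between costs and effects.

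The cost is a sentence or two of analysis wording and a regression inside the bootstrap loop. No new data are needed and trial conduct does not change.

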## Discussion

This lifestyle intervention was developed as a tool for prevention of CVD among those with an elevated risk. The content of the intervention is evidence-based and tailored to the target group. Furthermore, the intervention will exclusively be aimed at persons at risk for CVD, who may more likely be aware of the need to change behaviour. Counselling will be performed by professionals experienced in face-to-face counselling of this target group. Based on the literature and interviews with relevant stakeholders we designed a structured counselling protocol, incorporating MI strategies. Counsellors will raise awareness of the health problem and discuss determinants of behaviour change, to facilitate the participant in increasing importance, ability and readiness to change, and in changing actual behaviour. By applying the MITI, we will be able to report on the quality of MI in the intervention. The written information that will be given to the participants contains practical information and is easy to understand.

Several limitations of this study can however be mentioned. First, stress and other psychosocial problems will not primarily be addressed in the intervention, even though these factors are positively related to CVD risk. The counsellors were not trained in solving psychosocial problems. Stressful circumstances such as job strain, high work demands, and low job control that appear to be a barrier for behaviour change will however be discussed. Secondly, the intervention does not take place at company level. Therefore, the workplace environment cannot be changed, even though the environment has been shown an important determinant of health behaviour [37]. Furthermore, in an individually-based intervention study participants may lack the support of other participants or their employer, and the suggested 'toolbox meeting' cannot be used as a medium for the intervention. Finally, in the PHS only a limited number of variables is measured. Therefore, CRF will be derived from an indirect instrument that may be less accurate in predicting VO_2_max than a step-test or treadmill-test. For the same reason, waist circumference will not be assessed, even though abdominal obesity has been proven to be an important indicator for CVD risk [56,57].

Studying the effects of this intervention is important, as it aims at a serious and increasing health problem. This type of intervention has not been evaluated in this specific setting and in this target group yet. If proven effective, the employee will benefit from an improved lifestyle and a reduced CVD risk, and the employer may benefit from healthier workers and lower absenteeism. If proven cost-effective, in the future the OHSs in construction industry may implement this intervention on a larger scale.
